**Methods/design:**

MTFS-I expands on conventional measurement feedback systems for client outcomes by adding training in observational coding to promote EBT self-monitoring and focusing on implementation of EBT treatment techniques. It has two primary components. (1) The *training component*, delivered weekly in two connected parts, involves self-monitored learning modules containing brief clinical descriptions of core EBT techniques and mock session coding exercises based on 5–8 min video segments that illustrate delivery of core techniques. (2) The *feedback component* summarizes aggregated therapist-reported data on EBT techniques used with their active caseloads. MTFS-I is hosted online and requires approximately 20 min per week to complete for each treatment approach. This randomized trial will first collect data on existing delivery of family therapy and CBT techniques for youth in outpatient behavioral health sites (Baseline phase). It will then randomize site clinicians to two study conditions (Implementation phase): Training Only versus Training + Feedback + Consultation. Therapists will choose whether to train in family therapy, CBT, or both. Study aims will compare clinician performance across study phase and between study conditions on MTFS-I uptake, reliability and accuracy in EBT self-monitoring, and utilization of EBT techniques in treatment sessions (based on observer coding of audiotapes).

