## Methods/design

### Trial design

The trial design is a two-group randomized trial with baseline comparison: Following a 4-month Baseline phase, therapists working in behavioral health treatment sites will be randomized across two experimental conditions, Training Only versus Training + Feedback + Consultation, for a 1-year Implementation phase. During both study phases we will collect EBT fidelity data (therapist-reported checklists, session audiotapes); during the Implementation phase we will also collect MTFS-I uptake data (training and consultation activity). In Aim 1, by comparing Baseline versus Implementation data, we can examine the effectiveness of the MTFS-I training component for enhancing EBT fidelity across study sites, yielding proof-of-concept data in accord with the well-established Stage Model of behavioral treatment development [27]. In Aim 2, by experimentally comparing Training Only versus Training + Feedback + Consultation, we can test the added value of MBC procedures combined with expert consultation procedures [26] for enhancing MTFS-I benefits. Also the quasi-experimental analysis of Baseline data (averaged across all study therapists) versus Training Only condition data will shed light on the unique effects of the online training component, which is the most pragmatic feature of the overall MTFS-I package. Comparing averaged Baseline-phase data versus the Training + Feedback + Consultation condition will also provide insight on the full MTFS-I effects. It was not possible to include a no-intervention or waitlist control group because sites unilaterally preferred that all study therapists receive a clinically meaningful training experience. To maximize clinical utility and trainee motivation, each study therapist will select whether they want to train in FT, CBT, or both; training in both approaches will double the time commitment (to approximately 40 total min per week) for the given trainee. Figure 2 is the Standard Protocol Items: Recommendations for Interventional Trials (SPIRIT) diagram depicting the schedule of trial enrollment, interventions, and assessments. Additional file 3 presents the SPIRIT checklist. Study sites and eligibility, sample size, randomization, and contamination procedures.

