**Fig. 2 Fig2:**
[figure not shown]
SPIRIT diagram depicting the schedule of trial enrollment, interventions, and assessments

To host trial activities we will recruit four behavioral health outpatient clinics that attest to endorsing FT and CBT as staples of their clinical practice. All full-time clinicians will be eligible to participate. We project to enroll 32 therapists total (8 therapists per site [6 active slots plus 2 to replace dropouts]) treating 192 cases (24 therapist slots × 8 consenting cases/year). Treatment will average ~ 6 sessions/case (given routine therapy attrition), yielding ~ 1152 post-session therapist-reported checklists, about half with accompanying recordings (*n* ~ 576); half of these (~ 288 sessions) will be coded for EBT fidelity by research staff. Figure 3 shows a Consolidated Standards of Reporting Trials (CONSORT) flow chart of projected study enrollment. We will randomize volunteer therapists within each site to study condition at the start of the Implementation phase, given that MTFS-I procedures target individual therapists and their supervisors rather than entire agencies [24]. We will not randomize supervisors to condition, for two reasons. Because therapists in the Training Only condition will engage in solitary online training activities and will not review feedback reports or participate in expert consultation meetings with supervisors, we do not anticipate substantial supervisor “crossover” effects should a given supervisor oversee therapists in both conditions. Also, many clinics have only one supervisor, making it neither practical nor ecologically valid to randomize supervisors into condition. To guard against experimental contamination, supervisors will be asked not to review feedback reports in the presence of Training Only therapists.

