### Data analysis plan

Study data will have a three-level nested structure: clients within therapists within sites (we will average across sessions for each client). The basic analytic approach for these nested data will be multilevel mixed effects models examining the effects of Phase (Baseline versus Implementation) and Condition (Training Only versus Training + Feedback + Consultation) on dependent variables aggregated across each time period: 4-month Baseline phase (prior to MTFS-I training) and 12-month Implementation phase. We will use maximum likelihood estimation for continuous variables and robust weighted least squares for categorical variables. We will model Site and Therapist as random effects in all models. We will include Therapist (age, sex, race/ethnicity, experience, EBT attitudes, EBT proficiency) and Client (age, sex, race/ethnicity) factors at their respective levels to examine potential effects. Effect sizes will be calculated using the standardized *d* effect size indicator, interpreted as the standardized difference between contrasts for Phase and Condition comparisons [41]. Aim 1 exploratory contrasts will examine the Phase (within-subjects) effect, contrasting Baseline versus Implementation across all sites in EBT self-monitoring (reliability, accuracy) and EBT technique use (averaging across FT and CBT techniques). Aim 2 will experimentally test the Condition (between-subjects) effect on MTFS-I uptake, EBT self-monitoring, and EBT technique use.

To analyze EBT self-monitoring, reliability between therapists and observers on FT and CBT technique use will be calculated using the ICC_2,2_ [44]. Conditions will be compared on the relative magnitude of ICCs for each EBT scale. To compare conditions on therapist accuracy, we will use statistical equivalence testing methods, applying the confidence interval approach [45] to examine whether therapist scores are equivalent to corresponding observer scores. To analyze EBT technique use, a series of multilevel mixed effects models will be conducted with a dummy-coded Condition variable included at the Therapist level to test the contrast of main interest; alpha will be adjusted to account for multiple contrasts. For the Aim 1 analyses of Phase contrasts, a product interaction terms will be included to examine Phase by Condition effects; for significant interactions, we will test simple effects by examining Phase contrasts separately within condition.

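### Elected training track (FT, CBT or both) doubles the weekly load but is missing from the listed therapist covariates, leaving chance imbalance and avoidable variance in the Aim 2 comparisons

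*Protocol article*

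**What the plan says.** Under Trial design, every therapist picks an approach: "each study therapist will select whether they want to train in FT, CBT, or both; training in both approaches will double the time commitment". The Abstract gives the load per approach: the system "requires approximately 20 min per week to complete for each treatment approach". Electing both therefore brings it "to approximately 40 total min per week) for the given trainee".

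Allocation is described in the text after Figure 2: "We will randomize volunteer therapists within each site to study condition at the start of the Implementation phase". Site is the only grouping named. The numbers are in the same place: "We project to enroll 32 therapists total (8 therapists per site [6 active slots plus 2 to replace dropouts", which over four sites is 24 active slots.

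The Data analysis plan lists the adjustment factors: "We will include Therapist (age, sex, race/ethnicity, experience, EBT attitudes, EBT proficiency) and Client (age, sex, race/ethnicity) factors at their respective levels". Elected track is not among them. The same section says that "Aim 2 will experimentally test the Condition (between-subjects) effect on MTFS-I uptake, EBT self-monitoring, and EBT technique use". Trial design describes uptake data only as training and consultation activity, without saying how it is scaled for single- and double-track trainees.

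Two other sections bear on timing. Study measures says that the checklist items a therapist completes depend on the approach or approaches elected. The data collection section under Study procedures says that checklists are collected in both the Baseline and the Implementation phase.

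**The concern.** Both arms receive the online training, but its amount is not uniform: a therapist on both tracks is assigned twice the weekly modules and coding exercises of a therapist on one. If uptake is counted as activities or minutes, a fully compliant double-track therapist scores twice a fully compliant single-track one in either arm. Technique use may also vary with track, since the article expects the training itself to raise it.

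Track is thus a likely predictor of two Aim 2 outcomes, created by the design and known before allocation, yet absent from an explicit covariate list. With so few therapists per arm, a chance difference in track mix can move the estimated Condition effect in either direction. Variance due to track also widens the standard error when it need not.

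**Working it through.** **Timing of the choice.** Checklist items depend on elected track (Study measures). Checklists are collected during Baseline (Study procedures). Randomisation comes at the start of the Implementation phase (Trial design). Read together, track is fixed enough at Baseline to determine the form used, so it precedes allocation. The expected between-arm difference in track is then zero.

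**Chance imbalance.** The article gives no figure for this, so there is nothing to reproduce. From the article: 4 sites, with 6 active or 8 enrolled therapists each. Assumed: 1:1 allocation within site and half of the therapists electing both.

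- *Exactly half of each site electing both.* The number of double-track therapists in one arm at a site is hypergeometric; convolve over 4 sites.
  - 6 per site, 3 electing both, 3:3 allocation: 12 per arm. Arms split the 12 double-track therapists, so gaps come in steps of 2/12. A gap of 25 points or more means at least 4 of 12 (for example 8 v 4): probability .254.
  - 8 per site, 4 electing both, 4:4 allocation: 16 per arm. A gap of 25 points or more means at least 4 of 16: probability .314. A gap of one third or more: .092.
- *Each therapist electing both independently with probability p.* The SD of the gap is sqrt(2p(1−p)/n), with n per arm.

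| p | n per arm | SD of gap | P(gap ≥ 25 points) |
|---|---|---|---|
| .50 | 16 | .177 | .22 |
| .50 | 12 | .204 | .31 |
| .25 | 16 | .153 | .15 |
| .25 | 12 | .177 | .24 |

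Each point of gap is worth 0.20 min/week of scheduled training (20 min × gap). At p = .50 the SD is 20 × .177 = 3.5 min/week with 16 per arm and 20 × .204 = 4.1 with 12.

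**Type I error.** In simulated unadjusted t-tests with 16 therapists per arm, half electing both, and track effects of 0.3 to 3 between-therapist SDs, rejection under no Condition effect was 4.7% to 5.2%. Ignoring track leaves the test valid.

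**Precision, technique use.** Inputs from the Power analysis: 32 therapists, 6 × 1.5 = 9 sessions each, ICC .05. Assumed: two-sided alpha .05, half electing both, track effect δ in session SDs. Unadjusted track adds p(1−p)δ² = 0.25δ² to therapist variance:

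SE = sqrt(4 × (.05 + 0.25δ² + .95/9)/32), with power from the noncentral t on 30 df.

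| δ | SE | Power at d = .30 | Power at d = .40 |
|---|---|---|---|
| 0 (or track adjusted) | .139 | .55 | .79 |
| 0.2 | .144 | .52 | .77 |
| 0.3 | .149 | .50 | .74 |
| 0.5 | .165 | .42 | .65 |

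Using 28 df, to charge two for the covariate, changes the first row to .547 and .791. The baseline of .55 does not reproduce the article's power above .80 at d = .30. That is a separate matter and does not affect this comparison.

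**Precision, uptake.** Suppose uptake is a raw count, equal to a completion rate times 1 or 2 units, half electing both, with mean rate 1. Track variance is .25 and rate variance is 2.5 × CV². At CV .30 the track share is .25/(.25 + .225) = .53, and adjustment cuts the standard error by 1 − sqrt(1 − .53) = 31%. At CV .20 and .50 the cuts are 47% and 15%. These figures hold only for unscaled counts under assumed CVs. If uptake is a proportion of assigned work, the built-in two-fold difference disappears and so do they.

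**The case against.** A reader might infer that self-chosen load biases the comparison: a therapist allocated to the consultation arm could drop the second track, making training dose a consequence of arm. The documents do not support this. The checklist rule places the choice at Baseline, no text says therapists switch after allocation, and consultation is not necessarily weekly, since sites may choose weekly, bi-weekly or monthly formats. The article does not state that the choice is locked, but that silence is not evidence of switching.

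It can also be said that any unadjusted therapist characteristic may be imbalanced by chance, and that the planned Therapist random effect already carries track variance into the standard error. That is right and disposes of any claim about type I error. It does not recover the lost precision.

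Some further points stand. The article condenses a fuller protocol, so one may say only that no balancing on track is stated, not that none exists. Scaling of uptake may be settled elsewhere. A double-track therapist receives the same FT training as an FT-only therapist, so any track effect on technique use depends on the scale analysed; averaging over FT and CBT is stated only for Aim 1. Self-reported EBT proficiency, which is listed, covers allegiance to and skill in both approaches and may partly stand in for track.

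What remains is narrow: the covariate list is explicit, and it omits a two-fold difference in load that the design itself creates.

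**Conclusion.** The point holds as one of precision and chance imbalance. With half electing both, a gap of 25 points or more in double-track share arises in about 22% to 31% of allocations. It falls to 15% to 24% if a quarter elect both independently. For technique use, the cost of ignoring track is small if its effect is 0.2 to 0.3 SD (power at d = .30 falls from .55 to between .52 and .50) and larger at 0.5 SD (.42). For uptake, the cost depends on a definition the article does not give, and the 31% reduction in standard error should not be cited without its conditions. Election share, track effect, completion CV, allocation ratio and alpha are all assumptions, so the actual gain is unknown. The case for acting is that the information should already be on file and the adjustment costs almost nothing.

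**What to change.** 1. Record each therapist's track (FT, CBT, both) at Baseline, before randomisation. Therapists who enter later as replacements should have it recorded before their own allocation.
2. Add that track to the therapist-level covariates in the Aim 2 uptake and technique-use models. Three levels are preferable to single versus both, because FT-only and CBT-only therapists differ on each scale.
3. Analyse by the recorded track even if a therapist later changes it.
4. Express training uptake as the proportion of assigned modules and coding exercises completed.

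The cost is one or two therapist-level degrees of freedom and no new data collection. Balancing the allocation on track is optional: with 6 to 8 therapists per site the strata would be very small. Trial status reports that no participant had been enrolled when the article was written, so the change was still possible before the first allocation.

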**Fig. 2 Fig2:**
[figure not shown]
SPIRIT diagram depicting the schedule of trial enrollment, interventions, and assessments

To host trial activities we will recruit four behavioral health outpatient clinics that attest to endorsing FT and CBT as staples of their clinical practice. All full-time clinicians will be eligible to participate. We project to enroll 32 therapists total (8 therapists per site [6 active slots plus 2 to replace dropouts]) treating 192 cases (24 therapist slots × 8 consenting cases/year). Treatment will average ~ 6 sessions/case (given routine therapy attrition), yielding ~ 1152 post-session therapist-reported checklists, about half with accompanying recordings (*n* ~ 576); half of these (~ 288 sessions) will be coded for EBT fidelity by research staff. Figure 3 shows a Consolidated Standards of Reporting Trials (CONSORT) flow chart of projected study enrollment. We will randomize volunteer therapists within each site to study condition at the start of the Implementation phase, given that MTFS-I procedures target individual therapists and their supervisors rather than entire agencies [24]. We will not randomize supervisors to condition, for two reasons. Because therapists in the Training Only condition will engage in solitary online training activities and will not review feedback reports or participate in expert consultation meetings with supervisors, we do not anticipate substantial supervisor “crossover” effects should a given supervisor oversee therapists in both conditions. Also, many clinics have only one supervisor, making it neither practical nor ecologically valid to randomize supervisors into condition. To guard against experimental contamination, supervisors will be asked not to review feedback reports in the presence of Training Only therapists.

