### Power analysis

Power to detect an experimental effect is based on *n* = 288 audiotaped sessions coded. The study is optimally powered (exceeding .80) to detect a between-condition effect size of *d* = .30 (small) or greater when data are combined across sites. Power calculations were conducted using Optimal Design 3.01 [40]. With nested designs, power is substantially affected by number of sites as well as clusters (therapists and clients) within site [41], and less so by cases (sessions) within cluster. Aggregating across site, and assuming 32 therapists (*unit of randomization*) treating 6 clients each and submitting 1.5 taped sessions for review (*unit of analysis*) and moderately sized within-cluster intraclass correlation coefficients (ICCs) (*ρ* = .05) [42], yields optimal levels of power (exceeding .80) for even small effects (*d* = .30) and increasing power (exceeding .90) with effect sizes of *d* = .40 and greater. Previous research has yielded effect sizes *d* = .40–.50 using a similar design [43].

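### Power counts 32 therapists as randomised units although the sample-size paragraph provides 24 active slots plus 8 replacements; the stated power is not reached on either count

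*Protocol article*

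**What the plan says.** Under Trial design, the paragraph after Figure 2 gives the sample as 32 therapists in total: "8 therapists per site [6 active slots plus 2 to replace dropouts". The caseload is built on the slots, not on the head count: "treating 192 cases (24 therapist slots × 8 consenting cases/year". The same paragraph fixes the level and time of allocation: "We will randomize volunteer therapists within each site to study condition at the start of the Implementation phase". The opening of Trial design puts that point after Baseline: "Following a 4-month Baseline phase, therapists working in behavioral health treatment sites will be randomized across two experimental conditions".

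The Power analysis section uses another layout: "assuming 32 therapists (*unit of randomization*) treating 6 clients each and submitting 1.5 taped sessions for review". It adds "moderately sized within-cluster intraclass correlation coefficients (ICCs) (*ρ* = .05" and states power above .80 at d = .30 and above .90 from d = .40, on 288 coded tapes. The Data analysis plan treats Phase (Baseline versus Implementation) as an exploratory within-subjects contrast for Aim 1 and tests Condition between subjects for Aim 2.

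The text shown does not say when replacements enter, how they receive a condition, or whether they supply Baseline data.

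**The concern.** A replacement takes up work only when someone has left. With six slots at each of four sites, 24 slots are active when therapists are randomised. Thirty-two randomised units are reached only if leavers and their replacements are each counted as randomised, and the article describes no randomisation after the start of Implementation. In a therapist-randomised comparison the number of therapists drives precision, so the count behind the power statement matters.

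The second issue concerns Aim 1. A therapist who joins during Implementation has records in one phase only. In a mixed model those records enter the Phase estimate through comparison with other therapists, so turnover is mixed into what is labelled change within therapists.

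**Working it through.** **Head counts**

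- Therapists enrolled: 4 × 8 = 32. Active slots: 4 × 6 = 24. Replacements: 4 × 2 = 8.
- Clients: 24 × 8 = 192 in the sample-size paragraph; 32 × 6 = 192 in the power analysis.
- Coded tapes: 192 × 1.5 = 288, which is 288/32 = 9 per therapist or 288/24 = 12 per therapist.

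The totals agree, which hides the fact that the number of clusters does not.

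**Power inputs**

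From the Power analysis section: ICC ρ = .05, 288 tapes, d = .30 and .40. The article gives no numerical alpha, sidedness or allocation ratio; I assume two-sided .05 and 1:1. I give all 288 tapes to the Condition contrast, as the power analysis does.

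**Formula**

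For J therapists with m tapes each, the variance of the standardised difference is 4[ρ + (1 − ρ)/m]/J. Power comes from the noncentral t distribution on J − 2 degrees of freedom.

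**The plan's own layout, J = 32, m = 9**

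- Variance = 4 × (.05 + .95/9)/32 = 4 × .1556/32 = .01944; standard error .1394.
- d = .30: noncentrality .30/.1394 = 2.15, power .55 (stated: above .80).
- d = .40: noncentrality .40/.1394 = 2.87, power .79 (stated: above .90).

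**Active slots only, J = 24, m = 12**

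- Variance = 4 × (.05 + .95/12)/24 = 4 × .1292/24 = .02153; standard error .1467.
- d = .30: noncentrality 2.04, power .50.
- d = .40: noncentrality 2.73, power .74.

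| Layout | Power, d = .30 | Power, d = .40 | d at 80% power |
|---|---|---|---|
| 32 × 9 | .55 | .79 | .40 |
| 24 × 12 | .50 | .74 | .43 |

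The step from 32 to 24 costs .55 − .50 = .05 at d = .30 and .79 − .74 = .05 at d = .40. If 24 therapists supply only 9 tapes each (216 tapes), power at d = .30 is .43.

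**Can the stated power be recovered with 32 therapists?**

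- Normal approximation instead of t: .58 and .82.
- One-sided test: .68 at d = .30 with t, .69 with the normal approximation.
- ICC placed at client level only, none at therapist level: .68 at d = .30.
- Therapist-level covariates explaining all between-therapist variance: .72 at d = .30.
- No clustering, two-sided: .72 and .92.
- No clustering, one-sided: about .82 and .96.

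Of the variants tried, only the last meets both stated thresholds, and it ignores the therapist clustering that the power analysis says it includes.

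**The case against.** The best defence is that the two passages fit together. If leavers and replacements share the caseload of 24 slots, 32 therapists with 6 clients each is the natural result, and 32 is then the number of therapists contributing data. A replacement for someone lost during the four-month Baseline could be present when therapists are randomised. The article also gives a recruitment window of a year, which is compatible with staggered entry. The allocation of later entrants may be described in the full protocol or in the flow chart, neither of which is shown.

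Much of this stands. A missing allocation procedure is not a fault of a condensed article. The count is still unsettled: the power analysis calls all 32 the unit of randomisation, whereas the sample-size paragraph describes 8 of them as replacements and gives one time of randomisation. A replacement present at that time stands in for a leaver who was not randomised, so the number randomised then is still not 32.

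A reader might infer that all 8 replacements arrive after randomisation and inherit the leaver's condition, so that 8/32, a quarter of therapists, are allocated by who left which arm. The documents do not support this. They neither call randomisation a single event nor say that a replacement takes over the vacated condition. Inheritance is a risk to exclude, not a stated rule. Any figure for the resulting bias would need an assumed difference between replacements and leavers, which the documents do not supply.

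On Aim 1, the contrasts are labelled exploratory and a mixed model can handle unbalanced records. That limits the consequence, but it does not make a single-phase therapist informative about change within therapists.

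**Conclusion.** The point holds as a conflict over the number of randomised units behind a power statement that the design does not support. At ICC .05, with two-sided .05 and 1:1 allocation assumed, power is about .50 to .55 at d = .30 and .74 to .79 at d = .40, against the stated levels above .80 and above .90. A reader might blame the whole shortfall on counting replacements. That would be wrong: about 5 points come from 24 versus 32, and the rest is present with 32 therapists. The result depends on the assumed alpha, sidedness and ratio, and on any covariate or blocking inputs to the software that the article does not report; the variants tried that keep the clustering do not reach .80 at d = .30.

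For Aim 1, any replacement who joins after Baseline cannot inform the within-subjects Phase effect. How many would do so is not stated.

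**What to change.** 1. State how many therapists are randomised at the start of Implementation, and restate power on that number, or give the detectable d at 80% power (about .43 for 24, .40 for 32). State alpha, sidedness and allocation ratio with it. No added enrolment is needed.
2. If replacements are to count as randomised units, randomise them on entry within site and say so. The number of randomised therapists may then exceed 24, and the power statement should use the number expected.
3. Run the Aim 1 Phase contrast on therapists with data in both phases, and report the all-therapist version as a sensitivity analysis.

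The cost is a less favourable stated power and, if replacements are randomised on entry, slightly uneven arms within a site. The Trial status section says that no participants have been enrolled, so the change is to wording and the allocation list.
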